##### Primary Analyses of the Primary and Secondary Outcomes

All analyses will be conducted according to recommendations for cluster randomized crossover trials, accounting for clustering to ensure correct type I error rates and CIs [38,40]. In the case of a small number of clusters, mixed-effects regression and generalized estimating equation approaches are known to not perform well; analysis for FLUID will, therefore, be performed using cluster-level summaries. This method is known to perform well even with a very small number of clusters. Equal weight will be given to each cluster to obtain unbiased estimates for the cluster-average treatment effect. To implement the cluster-level method, binary outcomes will be expressed as proportions in each cluster-period and the differences (proportion under RL minus proportion under NS will be calculated for each cluster. These differences will then be analyzed using an unweighted linear regression model as described by Turner et al [41]. The t-distribution with degrees of freedom equal to the number of clusters minus 2 will be used. The intervention effect will be expressed as an absolute difference with 95% CI. To improve precision, the primary analysis will account for the following patient risk factors as fixed effect covariates: age, sex, comorbidity index, type of hospital admission (medicine, surgery, pregnancy and childbirth, and mental health), and admissions to ICU, using the 2-stage method recommended by Hayes and Moulton [42]. Patient age will be modeled using a restricted cubic spline to allow for the possibility of a nonlinear association. Mean imputation within hospitals will be used for missing baseline covariates. The same approach and covariates will be used for primary and secondary outcomes. The 2-stage method will be implemented as follows: (1) a multivariable regression model (logistic regression for binary outcomes and linear regression for length of stay) with the baseline characteristics as covariates but excluding the treatment and cluster indicators will be fit to the individual patient data in period 1 and period 2. Length of stay will be log-transformed prior to analysis. We will use each regression model to obtain predicted probabilities for each binary outcome and predicted length of stay for each patient. (2) For binary outcomes, we will calculate the expected number of events by summing the predicted probabilities across all patients in that cluster period; for length of stay, we will obtain the expected mean length of stay by averaging across all patients in that cluster period. (3) We will obtain residuals for binary outcomes by calculating the observed number of events minus the expected number of events divided by the number of patients in the cluster, and for length of stay by calculating the observed mean minus the expected mean. To estimate the treatment effect, the cluster-level method described above will then be applied to the residuals. Estimated intracluster correlation coefficients will also be reported [33]. The data presentation is indicated in Table 4.

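### Step 3 of the adjusted primary analysis names the wrong denominator for binary residuals: patients in the cluster (the whole hospital) instead of patients in the cluster-period

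*Protocol article*

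**What the plan says.** All of this stands in Primary Analyses of the Primary and Secondary Outcomes, except the definition of a cluster.

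- Unadjusted cluster-level method: "binary outcomes will be expressed as proportions in each cluster-period", and the difference, "proportion under RL minus proportion under NS will be calculated for each cluster", is analysed by unweighted linear regression. For the reference distribution: "The t-distribution with degrees of freedom equal to the number of clusters minus 2 will be used".
- Step 2 of the adjustment: the analyst will "calculate the expected number of events by summing the predicted probabilities across all patients in that cluster period".
- Step 3, binary outcomes: the residual is "the observed number of events minus the expected number of events divided by the number of patients in the cluster". For length of stay it is the observed mean minus the expected mean.
- Final step: "the cluster-level method described above will then be applied to the residuals".
- Reporting: "The intervention effect will be expressed as an absolute difference with 95% CI".

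Trial Design defines the clusters as the hospital sites. Each site runs both fluids, one per period.

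**The concern.** The section uses cluster-period and cluster as separate terms. The RL-minus-NS difference formed for each cluster can only be a hospital-level quantity. Read with the same meaning in step 3, the denominator counts patients from both periods while the numerator counts events from one. The result is not a difference in proportions, so it is on the wrong scale for the cluster-level method that follows.

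The scale matters in this trial. The main result is an absolute difference with its interval. Sample Size is built on a 1-point difference, and Conclusions frames the answer in the same terms. A real 1-point benefit shown as half a point, with an interval that is too narrow, could be judged smaller than the difference the trial set out to find.

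**Working it through.** **Inputs.** From Sample Size: 16 sites, 2 periods over 6 months, 1,500 patients per hospital per month, NS proportion 0.16, difference 0.01, within-period ICC 0.006, cluster autocorrelation 0.95. From the analysis section: t with 16 − 2 = 14 df.

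**The plan's own figure.** 3 months × 1,500 = 4,500 patients per cluster-period and 9,000 per hospital. 16 × 2 × 4,500 = 144,000, as stated.

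**Algebra.** In one hospital let n_R and n_N be the patients in the RL and NS periods, N = n_R + n_N and w = n_R/N. Let r_R = (O_R − E_R)/n_R, and r_N likewise.

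- Cluster-period denominator: D = r_R − r_N.
- Cluster denominator, as written: D* = w·r_R − (1 − w)·r_N.
- With w = 0.5 + δ: D* = 0.5·(r_R − r_N) + δ·(r_R + r_N).

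With equal periods δ = 0, so D* = 0.5·D in every hospital. The estimate, its standard error and the interval width are all halved, and t and P do not change. With unequal periods the second term lets part of the hospital's own level through, which the crossover would otherwise cancel, and this adds noise.

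**Worked hospital.** Take 4,500 patients per period, 16% events under NS and 15% under RL, and an expected rate of 15.5% in both periods.

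- NS: O = 720, E = 697.5, O − E = +22.5. RL: O = 675, E = 697.5, O − E = −22.5.
- Divided by 4,500: −0.005 − 0.005 = −0.010, the true difference.
- Divided by 9,000: −0.0025 − 0.0025 = −0.005, half of it.

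**Brackets.** Without brackets, the step 3 sentence could also be read as dividing only the expected count. For the NS period that gives 720 − 697.5/9,000 = 719.92, which is not a residual on any useful scale. The brackets therefore belong in the corrected text.

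**Simulation.** 3,000 runs per row, using the inputs above. Assumptions: hospital size varies around a mean of 4,500 per period, no covariates (expected events come from the pooled rate of the period), and the true difference is −1 point. The between-hospital SD of a period's share of patients is assumed, because the article gives no figure for it. In every row the ratio of the mean estimates (as written ÷ cluster-period) is 0.50.

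| SD of period share | Interval-width ratio | Rejection, cluster-period | Rejection, as written |
|---|---|---|---|
| 0 | 0.50 | 86.6% | 86.6% |
| 0.01 | 0.50 | 86.3% | 86.0% |
| 0.03 | 0.52 | 86.2% | 84.3% |
| 0.05 | 0.55 | 86.0% | 79.8% |

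With equal periods, the cluster-period denominator gives a mean estimate of −1.00 point, a mean 95% interval width of 1.28 points and coverage of 94.7%. As written, the figures are −0.50 point, 0.64 points and 13.4% coverage of the true difference. With no true effect and an assumed SD of 0.02, the rejection rate is 5.2% under both definitions.

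The factor of one half is algebra. The simulation adds only the coverage and the effect of unequal periods.

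**The case against.** The best defence is that the intended level is clear from context. Step 2 works per cluster-period. The length-of-stay half of step 3 rests on means over the cluster-period. The residuals feed a method defined on cluster-period proportions. Only a cluster-period denominator fits all of this, and the section names an established two-stage method. This stands: the phrase is most likely a slip, and the choice of method is sound.

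Three stronger readings are tempting, and the documents do not support them.

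- *The trial's estimate will be halved.* That follows only if the phrase is coded literally. No program is shown, and Results says the plan was written before the data set was received or any analysis done.
- *The error would pass unseen.* The P value would not reveal it, but Table 4 sets the percentages by fluid beside the absolute difference, Descriptive Analyses calls for cluster-period proportions, and the subgroup analyses are unadjusted and so on the full scale. A halved overall effect could be noticed there. This is only a partial safeguard, since covariate adjustment and equal weighting of hospitals give ready explanations for a gap.
- *Step 3 contradicts the unadjusted definition.* These are different quantities, a proportion and a residual. The mismatch is between step 2 and step 3.

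Context does not remove the point. The article presents itself as the protocol and analysis plan, and it gives no other definition of the binary residual. Timing of Final Analysis assigns the analysis to an independent statistician, supervised but not a coinvestigator, who should be able to follow the text as it stands.

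**Conclusion.** The point holds as an error in the stated formula, probably of wording. If followed literally, it multiplies each binary residual by the period's share of the hospital's patients. With periods of similar size, the absolute difference and its interval width come out at about half: a true −1.0 point becomes about −0.5. This applies to the primary outcome and all binary secondary outcomes. Length of stay and the unadjusted subgroup analyses are not affected.

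The superiority test is essentially intact. It is identical with equal periods and loses some power when the period share varies between hospitals (about 86% to 80% at an assumed SD of 0.05). Type I error showed no inflation in the one case examined. The harm is to the size and precision of the reported effect, and it depends on literal coding.

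**What to change.** In step 3, define the binary residual as (observed events − expected events) ÷ number of patients in that cluster-period. Keep the brackets: changing only the denominator would leave the sentence open to the reading in which only the expected count is divided. Then check that the analysis program uses this denominator for the primary and every binary secondary outcome.

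The cost is one phrase in the plan and one check of the code. No data are needed, and the design, estimand, weighting and degrees of freedom do not change.

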**Primary outcome, n (%)**					
	Composite of death and hospital readmission within 90 days of index admission				
**Secondary outcomes, n (%)**					
	Death within 90 days of index admission				
	Readmission to the hospital within 90 days of index admission				
	New dialysis within 90 days of index admission				
	Requirement for postoperative intubation in the postoperative assessment unit				
	Requirement for reoperation within 90 days of index admission				
	ED^a^ visit within 90 days within 90 days of index admission				
	Hospital length of stay, median (IQR)				
	Discharge to a facility other than home				

^a^ED: emergency department.

##### Subgroup Analyses

The primary outcome will be analyzed within the following subgroups of patients who are at a higher risk for exposure to fluids and with greater risk profiles and or severity of illness than other patients. These include age (<18, 18 to ≤65, 66 to ≤80, and >80 years); sex; type of hospital admission (medical, surgical, pregnancy and childbirth, mental health); elective and urgent or emergent surgical admissions, surgical admissions <24 hours, surgical subgroups (as described in Table 3); admission to ICU, infection alone and infection and organ dysfunction, infection alone and infection and organ dysfunction and ICU admission, trauma with injury severity score (ISS) ≥12, trauma with ISS=12 and ICU admission, traumatic brain injury, traumatic brain injury and ICU admission, and comorbidity index (Elixhauser) [43]. These subgroup analyses will be implemented without covariate adjustment and using the cluster-level summary method as described for the primary and secondary outcomes but applied to subgroup differences within each cluster. Results will be presented using forest plots.

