## Introduction

Crystalloid resuscitation fluids, including normal saline (NS) and Ringer’s lactate (RL), are among the most common interventions administered in hospitalized patients [1,2]. These fluids may be used as a life-saving measure to re-establish hemodynamic stability, replace fluid losses, and maintain intravascular volume.

In observational studies, NS has been associated with acute renal injury as compared to RL and other balanced crystalloid fluids, hypothesized to be due to higher chloride concentration and resultant metabolic acidosis that can occur with NS administration [3-5]. However, RL and other balanced crystalloid fluids with buffers have the potential to cause metabolic alkalosis [6,7] and theoretically, cause arrhythmias, tetany, coma, and seizures [8-10]. The lactate in RL may accumulate in the setting of liver failure and may influence clinical diagnoses and clinical decision-making [11-13]. Moreover, RL has a lower osmolarity in comparison to NS; when administered rapidly in large volumes, RL theoretically reduces plasma osmolarity and increases the risk of edema formation [14], which raises potential concern for patients with cerebral edema.

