In total, 2 large single-center multiple crossover trials conducted in the intensive care unit (ICU) and the emergency department (ED) among patients who did not require admission to the ICU, found that balanced crystalloid fluids as compared to NS were associated with lower major adverse kidney events at 30 days, which is a composite outcome of mortality, new renal replacement therapy, or persistent renal dysfunction [2,15]. In contrast, 2 large multicenter randomized trials (Balanced Solution versus Saline in Intensive Care Study [BASICS]; Plasma-Lyte 148 versus Saline [PLUS]) [16,17] examined the efficacy of NS as compared to a balanced crystalloid (RL and Plasma-Lyte 148 respectively) on the primary outcome 90-day mortality. Neither of these trials detected differences in 90-day mortality. In BASICS, the mortality rate was 22% versus 21.8%; and in PLUS, mortality was 27.2% versus 26.4% in patients receiving NS and RL, respectively. Renal function did not differ between the fluid groups in either trial, although the PLUS trial was stopped early due to recruitment challenges and insufficient funding during the pandemic. In a systematic review of 35,884 participants in 13 critical care trials published before January 2022, there were no detectable differences in renal function. In low-risk-of-bias trials, there was no significant difference in mortality for the NS as compared to the balanced crystalloid group (28.2% and 27.9% respectively; Relative Risk 0.96, 95% CI 0.91-1.01), nor renal function [15-28]. However, the authors concluded that there is a high probability that balanced crystalloids reduce death since the CIs ranged from a 9% relative reduction to a 1% relative increase in death.

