Crystalloid fluids are administered to the majority of patients admitted to the hospital and continued throughout their hospital stay. To address ongoing uncertainty on this topic, and address this evidence gap about fluid administered outside the ED and ICU, we designed a cluster randomized crossover trial. Our objective was to compare a hospital-wide strategy to preferentially stock NS or RL as the main crystalloid resuscitation fluid, aiming to have all admitted patients receive the allocated crystalloid from the time they enter hospital to hospital discharge, evaluating the primary composite outcome of death or readmission to hospital in the first 90 days. The design of the FLUID trial is novel because it involves a pragmatic cluster randomized crossover design, a waiver of patient informed consent to include all hospitalized patients, hospital-based randomization, and the use of routinely collected electronic health administrative data for the description of baseline characteristics and all study outcomes. FLUID will generate data at low risk of bias, providing key evidence about the consequences of crystalloid fluid on clinically important outcomes, and informing patient care and health care policy. It will also provide insight into a novel approach to the conduct of large pragmatic clinical trials.

This manuscript describes the protocol and statistical analysis plan for the evaluation of primary and secondary outcomes for the FLUID trial.

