**Assessments**										
	Demographics	✓								
	Case mix group	✓								
	Type of surgical admission	✓								
	Surgical subgroup	✓								
	Severity of illness	✓								
	Comorbidities	✓								
	Primary outcome									✓
	Secondary outcomes									✓

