**Severity of illness, n (%)**								
	Admission to ICU^a^							
	Infection Alone and Infection and Organ Dysfunction							
	Infection Alone and Infection and Organ Dysfunction and ICU admission							

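### Infection subgroups labelled by organ dysfunction and ICU admission may depend on the allocated fluid unless that status is fixed before exposure

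*Protocol article*

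**What the plan says.** Subgroup Analyses lists, among the groups in which the primary outcome will be compared, "infection alone and infection and organ dysfunction, infection alone and infection and organ dysfunction and ICU admission". The estimates use the cluster-level summary method without covariate adjustment and go into forest plots.

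Table 3 carries the first of these as a single row, "Infection Alone and Infection and Organ Dysfunction", in its severity-of-illness block, followed by one row that adds ICU admission. Table 1 (SPIRIT) ticks "Severity of illness" in the enrollment column, before allocation.

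The Introduction describes the strategy as "aiming to have all admitted patients receive the allocated crystalloid from the time they enter hospital to hospital discharge". It describes the data source as "the use of routinely collected electronic health administrative data for the description of baseline characteristics and all study outcomes".

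On mechanisms, the Introduction reports that in observational studies "NS has been associated with acute renal injury as compared to RL and other balanced crystalloid fluids", with a hypothesized chloride and acidosis pathway. It also says that "The lactate in RL may accumulate in the setting of liver failure and may influence clinical diagnoses and clinical decision-making". Of the two large multicenter trials it says "Renal function did not differ between the fluid groups in either trial". New dialysis within 90 days is a secondary outcome.

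**The concern.** A subgroup effect from a randomized comparison can be read causally when membership is settled before treatment can act. Here the allocated fluid is meant to begin at hospital entry, and the adherence section counts the emergency department among the settings where it is used. Organ dysfunction and ICU admission can follow that point. If one fluid changes how often infected patients are recorded with organ dysfunction, or how often they go to ICU, the two fluid periods place different kinds of patient on each side of the line. The comparison within each side then mixes the fluid's effect with a change in who is being compared. Covariate adjustment would not reliably undo this, and none is planned for the subgroups.

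These rows will draw attention, since the plan picks its subgroups for higher fluid exposure and greater severity. A row showing RL better or worse in infection with organ dysfunction could be taken as a finding about sepsis when it reflects only a shift in coding.

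**Working it through.** **1. Is status fixed before exposure?** Nothing in the article does so. The enrollment tick in Table 1 does not settle it: allocation is of hospitals, and analyzed patients are admitted in weeks 2 to 13 of each period, after allocation and run-in. Their severity cannot have been recorded in that column. The same Table 3 block also contains ICU admission, which can follow the start of fluid.

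**2. One group or several?** The wording allows two readings.
- *Separate strata* (infection alone; infection with organ dysfunction). Membership turns on organ dysfunction.
- *Pooled* (infection with or without organ dysfunction), as the single row in Table 3 may mean. Recoding organ dysfunction moves nobody in or out, so the bias from it is 0. The ICU version still conditions on an event after entry.

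**3. Size under the separate-strata reading.** The documents give no infection or organ-dysfunction figures, so there is no plan figure to reproduce. All inputs here are assumptions: under NS, 20% of infected patients are coded with organ dysfunction (90-day event risk 30%) and 80% are infection alone (risk 12%). Patients whose code depends on the fluid have risk 18%. RL avoids the code in a fraction s of infected patients and changes no outcome.

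- Organ dysfunction under RL: (0.20×0.30 − s×0.18)/(0.20 − s)
- Infection alone under RL: (0.80×0.12 + s×0.18)/(0.80 + s)

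| s | Organ dysfunction, RL | RL − NS | Infection alone, RL | RL − NS |
|---|---|---|---|---|
| 0.01 | 0.0582/0.19 = 30.63% | +0.63 points | 0.0978/0.81 = 12.07% | +0.07 points |
| 0.02 | 0.0564/0.18 = 31.33% | +1.33 points | 0.0996/0.82 = 12.15% | +0.15 points |

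The overall risk is the same in both arms (0.06 + 0.096 = 15.6%), so every difference in the table is spurious.

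**4. A second set of assumptions.** 30% are coded with organ dysfunction under NS. Risks are 40% (organ dysfunction under either fluid), 28% (under NS only) and 18% (under neither).
- No true effect, 1 to 5 points of extra organ dysfunction under NS: +0.40 to +2.00 points with organ dysfunction, +0.14 to +0.67 in infection alone. At 1 point: NS = (0.29×0.40 + 0.01×0.28)/0.30 = 39.6%, against 40% under RL.
- Opposite mechanism: lactate under RL adds 1 to 3 points of organ-dysfunction labels, again with no true effect. The differences are −0.39 to −1.09 points with organ dysfunction and −0.14 to −0.43 in infection alone.

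**5. Could a true effect change sign?** Suppose RL truly lowers risk by 1 point in every group. With the step 4 risks, the organ-dysfunction difference turns positive when the shift exceeds 0.01×0.30/(0.40 − 0.28) = 2.5 points. The threshold is 1.5 points if that risk gap is 20 points and 4.3 if it is 7. Infection alone needs about 7.8 points: 0.10s/(0.70 + s) = 0.01 gives s = 0.007/0.09.

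In a 16-cluster simulation with a 3-point shift and a true effect of −1 point, the mean estimate was +0.24 points with organ dysfunction and −1.00 in all infected patients. The all-infection group kept the right answer.

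**The case against.** **The split may not exist.** Table 3 shows one row, and a pooled group is immune to recoding of organ dysfunction. This stands, and the point is conditional on it. What remains is the ICU version and wording that leaves the choice open.

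**The timing may be fixed in a fuller plan.** A reader might infer that organ dysfunction is taken from the record of the whole stay. The article does not say so. It says only that baseline data are administrative, and a coding window could sit in a document that is not shown. So the claim is that membership may depend on treatment, not that it does.

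**The article's evidence is weaker than a causal claim.** It reports an observational association for NS. It ties lactate accumulation to liver failure and mentions clinical diagnoses in general, not organ dysfunction in infection. It also reports no renal difference in two large multicenter trials and in a systematic review. Against that, it cites two large single-center crossover trials with fewer major adverse kidney events on balanced fluids, and makes new dialysis a secondary outcome. The evidence is mixed. A subgroup definition should not be valid only if the fluids have no renal effect.

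**The sizes rest on assumptions.** This also stands. In step 3, s = 0.02 means that RL removes 2 of every 20 organ-dysfunction codes, or 10%. Pilot adherence (94% NS, 80% RL) gives a contrast in RL use of about 0.80 − 0.06 = 0.74, so the effect in patients actually exposed would have to be larger still. The infection-alone shifts are small, and the 1-point target belongs to the whole-population comparison.

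**Conclusion.** The point holds in conditional form. Unadjusted effect estimates are planned in infection groups labelled by two features that can follow fluid exposure, and the article shows nothing that fixes them beforehand. On the separate-strata reading, an assumed coding shift of 1 to 2 per 100 infected patients gives a spurious +0.6 to +1.3 points with organ dysfunction and +0.07 to +0.15 in infection alone. On the pooled reading, only the ICU version is exposed, and its size was not calculated.

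The net direction is unknown: extra organ dysfunction under NS makes RL look worse, while extra labels under RL make it look better.

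A reader might go further and infer that the subgroup effects will reverse sign. The documents do not support that. The illustration in step 3 assumes no true effect, so it cannot show a reversal. Step 5 shows that reversing a 1-point benefit is possible, but only with a shift of about 1.5 to 4.3 points in the organ-dysfunction stratum under assumed risks.

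The primary and secondary analyses do not use these subgroups, so this point leaves them unaffected.

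**What to change.** In Subgroup Analyses and Table 3:

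- State whether the infection groups are pooled or separate.
- Define the treatment-effect subgroup as all index admissions for infection, regardless of later organ dysfunction or ICU admission.
- If a severity gradient is wanted, take it from information recorded before fluid exposure, for example age, sex and diagnoses in prior ICES records.
- If the organ-dysfunction and ICU versions are kept, label them descriptive and do not present them as treatment-effect estimates.

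The cost is wording. The same ICES data serve, and the article says the plan was prepared before the trial data set was received. The downside is that the forest plot loses an effect row for infection with organ failure.

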**Age group, n (%)**								
	1 month to 18 years							
	>18 to 65 years							
	>65 to 80 years							
	>80 years							

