	**Trauma ISS^b^ ≥12, n (%)**							
		Trauma ISS≥12+ICU						

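### Subgroup analyses drop the covariate adjustment used for the overall result, at a small cost in precision, and two subgroup definitions disagree with Table 3

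*Protocol article*

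**What the plan says.** **Adjustment.** For the primary and secondary outcomes, the section Primary Analyses of the Primary and Secondary Outcomes states: "To improve precision, the primary analysis will account for the following patient risk factors as fixed effect covariates". The covariates are age, sex, comorbidity index, type of admission and ICU admission. A stage-1 regression that omits treatment and cluster gives each patient a predicted probability. Observed minus expected events, per patient in the cluster-period, then go into the cluster-level analysis.

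The section Subgroup Analyses covers the primary outcome only and departs from this: "These subgroup analyses will be implemented without covariate adjustment and using the cluster-level summary method as described for the primary and secondary outcomes". It gives no reason. Results go on forest plots.

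**Definitions.** The same section lists "trauma with injury severity score (ISS) ≥12, trauma with ISS=12 and ICU admission". The matching row of Table 3 reads "Trauma ISS≥12+ICU". The age subgroups are given as "age (<18, 18 to ≤65, 66 to ≤80, and >80 years", whereas the lowest age band in Table 3 is "1 month to 18 years" and the next band there begins above 18.

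**The concern.** The only reason given for adjusting is precision, and precision is scarcest in subgroups. Most of what adjustment needs is produced anyway, because stage 1 already yields a predicted probability for every patient.

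There is also a question of comparability. The overall effect is adjusted and the subgroup effects are not. Table 4 has one column for the absolute difference, and the sensitivity analyses described in the article do not include an unadjusted overall estimate. A reader who sets a subgroup beside the overall result cannot tell how much of any gap comes from the change of method.

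On definitions, the final analysis is to be run by an independent statistician who is not a coinvestigator (Timing of Final Analysis), so the written rule matters. Read literally, "trauma with ISS=12 and ICU admission" leaves out every ICU trauma patient with a score above 12. The age mismatch means that baseline counts and subgroup counts for two bands cannot agree if there are any 18-year-olds.

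**Working it through.** **The plan's own figure.** 16 hospitals × 6 months × 1500 patients per month = 144,000, as stated in Sample Size. One 12-week period is therefore taken as 3 × 1500 = 4500 patients per hospital. The article gives no precision figure for any subgroup.

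**Inputs from Sample Size and the primary analysis section.** Within-period ICC ρ = 0.006; cluster autocorrelation CAC = 0.95; 16 hospitals; t with 16 − 2 = 14 degrees of freedom (critical value 2.145); event rate p = 0.155, midway between 0.16 and 0.15.

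**Assumptions.** Stage-1 R-squared of 0.05 to 0.15. The trial-wide ρ, CAC and p carry over to subgroups. Adjustment reduces only the patient-level part of the variance.

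**Formula.** With m subgroup patients per hospital-period, the variance of one within-hospital difference is

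2p(1−p) × [(1−ρ)(1−R²)/m + ρ(1−CAC)].

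The 95% half-width is 2.145 × √(variance/16). The proportional narrowing from adjustment depends on m, ρ, CAC and R², but not on p or the number of hospitals.

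**Worked case, m = 4500, no adjustment.** 2p(1−p) = 2 × 0.155 × 0.845 = 0.26195. Patient part: 0.26195 × 0.994/4500 = 0.0000579. Cluster-period part: 0.26195 × 0.006 × 0.05 = 0.0000786. Sum: 0.0001364. Standard error: √(0.0001364/16) = 0.00292. Half-width: 0.63 points. With R² = 0.15 the patient part falls to 0.0000492 and the sum to 0.0001278. The ratio of standard errors is √(0.0001278/0.0001364) = 0.968, a narrowing of 3.2%.

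| Subgroup patients per hospital-period | Unadjusted half-width (points) | Narrowing, R² = 0.05 | Narrowing, R² = 0.15 |
|---|---|---|---|
| 4500 | 0.63 | 1.1% | 3.2% |
| 1000 | 0.99 | 1.9% | 5.9% |
| 200 | 1.99 | 2.4% | 7.3% |
| 50 | 3.90 | 2.5% | 7.7% |

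For very small subgroups the narrowing tends to 1 − √(1−R²), that is 2.5% and 7.8%. This is worth 1/(1−R²) − 1, or about 5% and 18%, more patients. The first row is a whole hospital-period, so it bounds the largest subgroups.

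**Definitions side by side.**

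- Trauma: the parent subgroup is "trauma with injury severity score (ISS) ≥12". The next item, which adds ICU admission, has an equals sign in place of ≥. Table 3 has ≥ for both.
- Age: 18-year-olds are in the second band in Subgroup Analyses and in the first band of Table 3. With age in completed years, the other cut-points coincide.

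**The case against.** The strongest reply is that unadjusted subgroups are an open, prespecified choice. The article justifies adjustment by precision alone, and an unadjusted within-hospital difference remains a valid estimate. That stands: a reader might infer error or bias, and the documents support neither.

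The gain is also modest and rests on an assumed R-squared. At 50 patients per hospital-period, adjustment moves the half-width from 3.90 to about 3.6-3.8 points, still far wider than the 1-point target difference. Subgroup size matters much more than adjustment. Several subgroups are defined by an adjuster (age, sex, admission type, ICU, comorbidity), so that covariate has little left to explain within them. All of this stands and limits the point to a refinement.

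Two further inferences are tempting. One is that case-mix shifts between periods are largest in subgroups; nothing in the article shows this. The other is that the forest plot will carry the adjusted overall effect; the article does not say which overall estimate, if any, it will show. The difference of basis holds without either.

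On trauma, one might conclude that a wrong subgroup was intended. The correct sign immediately before it and in Table 3 makes a typographical slip much the likelier reading. On age, Subgroup Analyses defers to Table 3 only for the surgical subgroups, so this is a disagreement between two lists and not a breach of a governing definition.

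**Conclusion.** The point holds as a minor one. The subgroup estimates are valid but somewhat less precise than the planned method allows, and they are on a different basis from the adjusted overall estimate. For an assumed R-squared of 5-15%, the avoidable width is about 1-3% in the largest subgroups and up to about 2.5-8% in small ones, less where an adjuster defines the subgroup. If adjustment also removed some cluster-period variation the gain would be larger, but the documents give no basis for assuming that.

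The ISS=12 wording contradicts its own sentence and Table 3, and needs correcting. The age-18 mismatch is a matter of consistency only. It would be wrong to say that the definition conflicts make the subgroup results noisier in general: only the literal ISS=12 reading shrinks a subgroup, and the age boundary does not affect precision. The primary analysis is untouched by any of this.

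**What to change.** 1. Compute subgroup effects by averaging stage-1 observed-minus-expected values within subgroup and cluster-period, then apply the same cluster-level method. Use the same stage-1 covariate set as the overall analysis. If ICU admission is dropped because it may follow fluid exposure, drop it from both; otherwise the subgroup and overall estimates would again rest on different adjustments.
2. Report the unadjusted subgroup results as a supplement, with an unadjusted overall estimate beside them.
3. Change ISS=12 to ISS≥12 in the trauma-with-ICU subgroup.
4. Use one set of age cut-points in Subgroup Analyses and Table 3.

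The cost is plan wording and a few lines of code, plus one refit of stage 1 if ICU admission is removed. The downside is some dependence of the subgroup results on the stage-1 model, although miscalibration that is the same in both periods cancels in the within-hospital difference. The article says that the plan was written before the data set was received; changes made before receipt could not appear data-driven.
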